## 8. Methods for Assessing Efficacy and Safety

### Appraisal of the Risk-to-Benefit Ratio

In the many EPO trials both in preterm infants and in adults EPO was well tolerated. Adverse effects described in adults are arterial hypertension, polycythaemia, thrombosis and antibody formation against EPO-receptors. As preterm infants tend to have low blood pressure, anaemia and delayed coagulation these side effect of EPO may even be beneficial. Antibody formation occurred in kidney patients after long-term subcutaneous administration of EPO and therefore is very unlikely to be a problem in preterm infants after three intravenous injections. Carcinogenicity finally was observed exclusively in cancer patients who received EPO to treat anaemia, which is hardly relevant for preterm infants.

One retrospective study reports a higher incidence of retinopathy of prematurity in preterm infants treated over 6 weeks with EPO to prevent anaemia compared with controls. This finding could not be confirmed in other prospective randomised controlled trials.

In summary EPO, is considered to be safe. To eliminate the minimal doubts, during this trial infant will be monitored continuously and all adverse events noted and sent to the sponsor at day 10. The safety board will continuously monitor the adverse events and stop the trial if significantly more complications ( $p < 0.01$ ) occur in the verum group.

The nature and extent of the therapeutic interventions employed within the study described here do not go beyond what is therapeutically required for these patients.

### Methods for Assessing Efficacy

Primary endpoint: At 24 months of age corrected for prematurity Bayley Scales of Infant Development (BSID-II) and the presence or absence of impairment of motor function (cerebral palsy) and neurosensory function (blindness or deafness) will be assessed.

Secondary endpoints:

- ultrasound of the brain will demonstrate if Epo reduces the incidence of brain damage, specified as intracranial haemorrhage graded after Papile, ventricular dilatation and white matter disease (periventricular echodensities).
- the occurrence of mortality, septicaemia, necrotising enterocolitis, bronchopulmonary dysplasia (oxygen dependency at 36 weeks postmenstrual age) and retinopathy will be documented in each infant.

- MRI at 40 weeks to assess (a) increased myelinated white matter volume (by quantitative volumetric MRI) (b) microstructural development (by diffusion tensor MRI) of cerebral white matter and (c) cortical and subcortical (basal ganglia) gray matter volume (by quantitative volumetric MRI). This examination will only be optional.

### **Adverse Events (AE), Definition**

Adverse events are taken to be any general lack of well-being, symptoms of illness, laboratory parameters outside the normal range and other impairments observed within the context of a clinical study. This applies regardless of any causal connection with the investigational study drug administered.

Any event not attributable to the category „serious“ (see section 8.4) is considered an adverse event (AE).

### **8.4 Serious Adverse Events (SAE), Definition**

A serious adverse event (SAE) is any event that is life-threatening or fatal

- results in significant or permanent disability results in a tumour disease or malformation
- meets any other comparable criteria

Such events are considered serious, regardless of any causal connection with the investigational study drug administered.

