| Calculation of case numbers | 176 cases per group (2-sided alpha 0.05, power 0.8)                                                                                                                                                                                                                                                                                                                                                                                                                                                                                                                                                                         |
| Study duration              | Scheduled starting date: 01/2006
Prospective total duration of study 24 months + 24 mths follow-up
Study duration (clinical part) / patient max. 16 weeks until 40. th week of gestation                                                                                                                                                                                                                                                                                                                                                                                                                   |
| Question                    | Does erythropoietin reduce brain, eye, lung and gut damage and ameliorate the neurodevelopmental outcome in preterm infants?                                                                                                                                                                                                                                                                                                                                                                                                                                                                                                |

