| Primary Objective           | Mental development at 24 months (Bayley II)                                                                                                                                                                                                                                                                                                                                                                                                                                                                                                                                                                                 |
| Secondary Objectives        | 
 
1. Incidence of intracranial haemorrhage
 
2. white matter disease (periventricular leucomalacia)
 
3. septicaemia
 
4. necrotising enterocolitis
 
5. persistent ductus arteriosus (PDA)
 
6. bronchopulmonary dysplasia
 
7. retinopathy
 
8. Length of stay in hospital
 
9. Cerebral volume at 40 postmenstrual weeks (MRI)
 
10. Weight, length and head circumference at 40 postmenstrual weeks and 24 months after term
 
11. Incidence of visual, hearing and motor impairment at 24 months
 
 |
| Inclusion Criteria          | 
 
1. Infants born between 260/7 and 316/7 gestational weeks
 
2. Postnatal age less than 3 hours
 
3. Informed parental consent (preferably obtained before birth)
 
                                                                                                                                                                                                                                                                                                                                                                      |

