## 1.6 Time table

| Point(s) of time
Action         | Before start of study | In Hospital |             |                             |                | Follow-up         |                                     |
|------------------------------------|-----------------------|-------------|-------------|-----------------------------|----------------|-------------------|-------------------------------------|
|                                    |                       | Day 1 -3    | Day 7 to 10 | Every two gestational weeks | Discharge home | Gestation week 40 | 24 months corrected for prematurity |
| Inclusion criteria                 | •                     |             |             |                             |                |                   |                                     |
| Exclusion criteria                 | •                     |             |             |                             |                |                   |                                     |
| Demographic data                   | •                     |             |             |                             |                |                   |                                     |
|                                    |                       |             |             |                             |                |                   |                                     |
| Vital signs                        |                       |             |             |                             |                |                   |                                     |
| Continuous monitoring  | •                     | •           | •           | o                           |                |                   |                                     |
| Laboratory                  |                       |             |             |                             |                |                   |                                     |
| Blood count            | •                     | o           | •           | o                           |                |                   |                                     |
| Clinical chemistry     | o                     | o           | o           | o                           |                |                   |                                     |

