| Catecholamines                     | •                     | •           | •           | •                           |                |                   |                                     |
| other medication       | •                     | •           | •           | •                           |                |                   |                                     |
| Study medication            |                       |             |             |                             |                |                   |                                     |
| administration of investigat. drug |                       | •••         |             |                             |                |                   |                                     |
| Adverse events                     |                       | •           | •           | •                           | •              |                   |                                     |
| Serious adverse events             |                       | •           | •           | •                           | •              |                   |                                     |
| Confirmation of completeness       |                       |             |             |                             | •              |                   | •                                   |

- compulsory (for medication, adverse events etc indicate „no“ if none), o optional
- Continuous monitoring: heart rate, pulse oximetry, (optional: transcutaneous pO2 and pCO2, arterial blood pressure, cerebral oxygenation with Near infrared Spectroscopy [NIRS] optional)
  - Blood counts: haematocrit; leucocytes, thrombocytes and differential blood count only when medically indicated
  - Clinical chemistry: Na, K; creatinine, urea (only when medically indicated))
  - Epo concentration in umbilical cord serum
  - Other medication: aminophylline, caffeine, insuline, indomethacine or ibuprofen, steroids etc.

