#### **4.3 Study duration**

The study is scheduled to begin on 01 January 2006. The in-hospital phase of the study will last minimum 8 weeks, maximum 14 weeks (until 40 completed weeks of gestation). All patients will

be followed up for developmental outcome at 24 months after term and at five years. Therefore the whole study will last five years for each participating child.

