## 7.6 Individual End of the Study

The end of the study for each patient will be death, discharge home or gestational age of 40 (+4 weeks) completed weeks.

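### Scheduled AE/SAE collection stops at discharge home, while the SAE definition and reporting rule have no end date; some late events have no planned capture, and the safety window ends on a date that is itself an endpoint

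*Protocol*

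**What the plan says.** The last three columns of the time table (protocol 1.6) are "Discharge home | Gestation week 40 | 24 months corrected for prematurity". The row for "Serious adverse events" and the row for adverse events carry the compulsory mark at day 1-3, day 7-10, every two gestational weeks and discharge home. Both are blank in the last two columns.

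Section 7.6 agrees with that cut-off: "The end of the study for each patient will be death, discharge home or gestational age of 40 (+4 weeks) completed weeks". Section 4.3 does not. There all patients are to "be followed up for developmental outcome at 24 months after term and at five years", and the study is said to last five years for each child.

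Section 8.4 defines an SAE without any time limit. Besides fatal and life-threatening events it includes one that "results in significant or permanent disability results in a tumour disease or malformation", whatever the cause. Section 8.5 requires SAEs to reach the sponsor within 24 hours and states no date on which this duty ends.

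The synopsis lists "Length of stay in hospital" as secondary objective 8. The risk-to-benefit section (8.1) has all adverse events sent to the sponsor at day 10. It also has the safety board stop the trial if complications are significantly more frequent on verum at p < 0.01.

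**The concern.** Two things follow if the time table and 7.6 are applied as written.

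First, an investigator who learns of a tumour or a life-threatening illness after discharge cannot tell whether it is reportable. Sections 8.4 and 8.5 point to yes; 1.6 and 7.6 point to no. Nothing prompts anyone to ask, although every child is seen again at 24 months. An analysis plan cannot recover events that were never recorded.

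Second, the AE window closes on a date that the treatment might move. The hypothesis in 3.1 is that EPO reduces injury to brain, eye, lung and gut, so an effect on stay is conceivable. An arm that goes home sooner is watched for less time and shows fewer events at the same underlying rate. A shorter stay on verum could hide an excess; a longer stay could create an apparent one.

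**Working it through.** **Window length.** The inputs are gestational age at entry, 26 0/7 to 31 6/7 weeks (5.2), and an end at 40 completed weeks (4.3).

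- Longest: 40 - 26 = 14.0 weeks.
- Shortest: 40 - 31 6/7 = 8.1 weeks.

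This reproduces 4.3: "The in-hospital phase of the study will last minimum 8 weeks, maximum 14 weeks (until 40 completed weeks of gestation". The synopsis gives "max. 16 weeks until 40", which does not follow from the same inputs: the maximum is 14 weeks to week 40, or 18 with the additional 4 weeks in 7.6. So 8 to 14 weeks is time from birth to week 40; discharge earlier than that shortens the window.

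**Share of follow-up covered.** Take 24 months as 104.4 weeks and five years as 260.9 weeks after term.

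- To 24 months corrected: 8.1/(8.1 + 104.4) = 7%; 14/(14 + 104.4) = 12%.
- To five years: 8.1/(8.1 + 260.9) = 3%; 14/(14 + 260.9) = 5%.

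**Effect of one week less stay on observed time.** 1/14 = 7%; 1/8.1 = 12%. The week lost is the last one before discharge. If events cluster in the first days, the share of events lost is smaller, so 7-12% is then an upper bound.

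**Effect on an arm comparison (illustration).** Assumptions that the protocol does not supply: the same constant hazard in both arms, a cumulative AE proportion p of 20% or 50% over a window of W weeks, and a window d weeks shorter in one arm. The shorter arm then shows 1 - (1 - p)^((W - d)/W). For example, with W = 8, p = 50% and d = 1: 1 - 0.5^(7/8) = 45.5%, a difference of 4.5 points with no true effect. The last column is the chance that one comparison of 210 per arm (420/2) reaches two-sided p < 0.01 in the direction of that difference. With equal windows it is 0.5%.

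| W (weeks) | p | d (weeks) | Spurious difference (points) | Chance of p < 0.01 |
|---|---|---|---|---|
| 8 | 20% | 1 | 2.3 | 2.4% |
| 8 | 50% | 1 | 4.5 | 5.0% |
| 14 | 20% | 1 | 1.3 | 1.2% |
| 14 | 50% | 1 | 2.5 | 2.0% |
| 8 | 20% | 2 | 4.6 | 8.9% |
| 8 | 50% | 2 | 9.5 | 26.4% |
| 14 | 20% | 2 | 2.6 | 2.9% |
| 14 | 50% | 2 | 5.2 | 6.6% |

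**What is captured after discharge, by type of event in 8.4.**

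- Permanent disability: cerebral palsy, blindness, deafness and graded disability are assessed at 24 months, with neurological, visual and hearing examinations at five years (7.8). These are outcome data, without the causality assessment that 8.5 asks for.
- Death: mortality is to be documented in each infant (8.2), with no time point given.
- Tumour disease and non-fatal life-threatening events: no scheduled capture.

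**The case against.** Several stronger readings are tempting, and the documents do not support them.

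- A reader might infer that the late SAEs are simply not collected. Permanent disability is assessed systematically at 24 months and five years, and deaths should surface through the mortality endpoint and the planned visits. Readmission is not a named criterion in 8.4.
- A reader might infer that late events can never enter SAE reporting. Section 8.5 has no end date, so a late SAE may still be reported spontaneously. The time table is also not a full list of follow-up data: it has no row for the Bayley test, although that is the primary endpoint. A blank cell there is weak evidence alone. It carries more weight beside 7.6, and because the completeness row in the same table is marked both at discharge and at 24 months.
- A reader might infer that the arms are compared unfairly. The spread of windows between infants of 26 and 31 weeks is balanced in expectation by randomisation. Bias needs a real difference in stay between arms, and nothing in the protocol shows one.
- A reader might assume discharge at about 36 weeks and put the loss at 14% (one week of an assumed mean of seven) to 24% (one week of 4.1). The protocol gives no discharge age, and windows of 4.1 and 7 weeks lie below the 8-week minimum in 4.3.

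The other side also has a real point on early safety. The three doses fall within the first 42 hours, the AE transfer at day 10 gives every infant one common window, and bronchopulmonary dysplasia is judged at a fixed 36 weeks. However, AE recording continues past day 10, and 8.1 does not say which window the p < 0.01 comparison uses. The common window therefore exists, but the comparison is not tied to it.

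**Conclusion.** The point holds in limited form. Scheduled AE/SAE recording ends at discharge home, and five places in the protocol disagree on how long SAEs are to be reported. Tumours and non-fatal life-threatening events after discharge have no planned capture, and for death the time point is open. Even a window that runs to week 40 covers only about 7-12% of the time to the 24-month endpoint.

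Unequal windows between arms are a possibility, not a demonstrated bias. One week less stay would remove about 7-12% of observed time on the protocol's 8 to 14 weeks. With assumed event rates of 20-50% and a constant hazard, that is a spurious difference of about 1 to 5 percentage points. It shrinks if events cluster early; a window cut short by discharge before week 40 would make it larger, by an amount the protocol gives no basis to estimate. This is a cheap improvement, not a flaw that invalidates the safety assessment.

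**What to change.** 1. Reconcile 1.6, 4.3, 7.6, 8.4 and 8.5 so that they state one SAE reporting period. In the same edit, reconcile the 16 weeks in the synopsis with the 14 weeks in 4.3.
2. Mark SAE at gestation week 40 and at 24 months in the time table.
3. At the existing 24-month visit, record deaths and any other event since discharge that meets the 8.4 definition.
4. Compare AEs and SAEs between arms over one fixed window common to all infants, for example to 40 weeks postmenstrual age, and name the window used for the p < 0.01 rule in 8.1.

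The cost is wording in the protocol and data collection form, a few questions at a visit already planned, and one contact at term for infants already home. The term MRI is optional, so it cannot serve as that contact for everyone. Interval events would rest partly on parents' reports, which is a small drawback.

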### **SAE, AE: Evaluation, Assessment, Documentation**

Adverse events (AE) and serious adverse events (SAE) are documented in the data collection form.

For each adverse event, the investigator will assess the degree of severity, the intensity, and the connection with investigational study drug; the onset and the end of the event, as well as the counteractive measures taken and the further course of the event, will be documented by the investigator.

Serious adverse events (SAE) have to be reported to the Sponsor within 24 hours by the PI; the Sponsor will then take charge of further reporting procedures as required by the HMG and VKlin. Such a report to the Sponsor can be done by [contact]), [contact] or [name]) or by e-mail ([contact]). For documentation purposes, a special form is provided along with the data collection form.

### **8.6 Premature Termination of the Clinical Trial**

For the patients' benefit and in their best interest, the Principal Investigator (PI) or an individual investigator may terminate the study within their area of responsibility at any time. In this case, the appropriate Ethics committee will be notified immediately.

## 9. Information on Statistics, Evaluation

### 9.1 Number of Cases, Statistical Considerations

**Diagram:** theoretical patient recruitment and progress

[figure not shown]

### Biometric Planning and Data Evaluation

Analysis of the data will be done after inputting all the data, after plausibility checks and termination of monitoring (data lock), at the earliest from spring 2009 and no later than spring 2013.

First the success of randomisation will be documented by checking the treatment groups for uniform composition with regard to age, sex, body weight, and degree of prematurity. For this purpose, a table will be created with measures of location and scatter, depending on the type of scale. Subsequently, the parameters needed to test the hypothesis on the primary objective will be estimated as described above. It will be attempted to take into account the influence of known risk factors for brain damage, as well. Next, the secondary objectives will be described in their dependence on the influencing and disturbance variables. Simple models of variance analysis will be used to describe the central tendency. 99% confidence intervals will be given for effects, so that a high confidence level can also be obtained when interpreting several effects. The secondary target variables will be transformed where necessary (e.g. take logarithms of concentrations) so that the assumptions of the linear model are justified. The results will be transformed back onto the original scale. Example: geometric mean as an estimate of the median and coefficient of variation as an indication of relative error.

Kaplan-Meier curves will be provided for durations of stay. For binomially distributed target variables, a logic regression will be applied.

## **Interim Analysis**

After treatment of the first 45 patients, the sponsor will draw up a report on the adverse events and the serious adverse events plus the group sizes, which he will then discuss with the safety board. The report, as well as the minutes of the discussion and any potential consequences from this, will be communicated in writing to all study centres.

